## Abstract

**Aim:** High prevalence of metabolic disorders causes higher risk of cardiovascular diseases after kidney transplantation (KT), which remains the main burden impairing short-term and long-term survival. This open-label, prospective, randomized, 3-arm, controlled trial will evaluate the safety, tolerability and efficacy of metformin and empagliflozin in ameliorating metabolic profiles after KT.

**Methods:** After a screening assessment, eligible patients with an estimated glomerular filtration rate (eGFR) >45 mL/min/1.73m2 are randomly assigned to standard triple immunosuppression alone, standard immunosuppression plus metformin (500 mg twice daily), standard immunosuppression plus empagliflozin (25 mg once daily) from discharge. The primary endpoint is the differences in the visceral-to-subcutaneous fat area ratio over 12 months, evaluated by magnetic resonance imaging (MRI). Secondary outcomes include kidney graft function, glycometabolism, lipid metabolism, and inflammatory parameters. The trial will enroll 105 kidney transplant recipients, providing 90% power to detect the difference at 5% significance.

## Introduction

Advances in patient selection, organ procurement and preservation, surgical technique, immunosuppression, and infection prevention have conferred significant improvement in rejection, infection, and subsequently decreased cause-specific graft failure rates after kidney transplantation (KT) (1). However, cardiovascular diseases (CVD) remain the main burden impairing both short-and long-term patient survival (2). Compared with the general population, conventional CVD risk factors, including obesity, liver and muscle insulin resistance, dyslipidemia, hypertension, and diabetes mellitus, are all highly prevalent in this population for long-term exposure to steroids and calcineurin inhibitors (3–6).

Previous studies demonstrated that adenosine 5′-monophosphate (AMP)-activated protein kinase (AMPK) is a central regulator of multiple metabolic pathways and a key player in regulating cellular energy metabolism (7, 8). Activation of AMPK by pharmacological agents may hold a considerable potential to reverse the metabolic abnormalities in chronic metabolic diseases (9, 10). Metformin, a widely used antidiabetic drug, acts as an AMPK activator by inhibiting complex I of the mitochondrial electron transport chain in many tissues, including adipose, skeletal muscle, and heart (11). A recent small clinical trial observed that metformin administration can safely ameliorate metabolic profiles in glucocorticoid-treated patients with inflammatory disease but without pre-existing diabetes (12). In addition, another antidiabetic drug sodium-glucose-cotransporter-2 (SGLT-2) inhibitors can improve metabolic parameters and cardiovascular risk in patients with or without diabetes in pre-clinical and clinical studies (13, 14, 14, 15). Another small clinical trial even reported that compared to metformin, significant improvement in anthropometric parameters and body composition, in overweight and obese women with polycystic ovary syndrome after treatment with empagliflozin (16). Hence, metformin and SGLT2 inhibitors may be used as potential adjuvant therapies to improve metabolic disorders after KT.

Although several preliminary clinical trials showed that metformin and SGLT-2 inhibitors can be used safely and improve glucose control after KT, but they are small-sample sized and only include patients with diabetes (17–19). We will conduct a prospective clinical trial with the aim of exploring their roles in improving metabolic profiles.

## Methods and Analyses

### Study Design

This study is designed as a 12-month, single-center, prospective, 3-arm, open-label, randomized clinical trial (Figure 1). This study has been registered at www.clinicaltrials.gov (NCT05013112) and is conducted in accordance with the Declaration of Helsinki and local regulations. Selected patients are recruited if they meet the following inclusion criteria: (1) living-donor kidney transplantation; (2) eGFR level > 45 ml/min/1.73m2 at discharge; (3) 18 < Age <65 years; (4) receiving standard triad immunosuppressive regimen. Our key exclusion criteria are as follows: (1) previous therapy with metformin or SGLT 2 over the previous 3 months; (2) pre-transplant diabetes; (3) alanine aminotransferase (ALT) or aspartate aminotransferase (AST) > 2.5 or more of upper limit of normal; (4) Combined with HBV/HCV/HIV infection in the donor or recipient; (5) Malignancy history in the donor and recipient; (6) organ transplant history in the recipient. In addition, patients will exit from this clinical trial: (1) Serious deviation from clinical trial protocol; (2) Due to serious adverse reactions, the drug must be stopped in advance; (3) Withdrawal of informed consent; (4) Poor compliance and failure to use drugs as planned; (5) Lost to follow up.

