### Statistical Analysis

Two populations will be used in the analyses. The intention-to-treat (ITT) population will include all participants who have been randomly assigned, whereas the per-protocol (PP) population will include all participants who accomplish the entire intervention. The baseline characteristics of the study will be summarized as the means ± standard deviations for parametrically distributed data, geometric mean values (and 95% confidence intervals) for non-parametrically distributed data, and numbers (percentages) for categorical data.

Differences between participants who complete and withdraw from the trial will be analyzed by using a Student *t*-test or the Mann–Whitney test for continuous variables (e.g., age) and the chi-squared test for categorical variables (e.g., sex). For clinical outcomes, analysis of covariance will be used to examine differences among three groups, adjusting for potential confounding factors and effect modifiers (e.g., baseline age and sex). Based on the literature, some patients have higher risk of post-transplantation diabetes mellitus (PTDM), including those with family history of diabetes; or polycystic kidney disease; or age ≥60 years; or age 45–59 years plus (i) triglycerides ≥200 mg/dL; (ii) triglycerides 150–200 mg/dL and body mass index >27 kg/m2; (iii) triglycerides 150–200 mg/dL and high density lipoprotein (HDL) <40 mg/dL (men)/ <40 mg/dL (women) Hence, subgroup analysis will be conducted based on the risk of PTDM, and was also conducted based on the components of the criteria for high-risk PTDM (26–28). Our statistical analysis will be performed by using R software, and the results will be considered significant at a *P*-value of < 0.05.

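### The exit rules do not separate stopping study drug from leaving the trial, so the all-randomised set lacks later primary-outcome data for patients who stop, comply poorly or seriously deviate

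*Protocol article*

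**What the plan says.** All places are in the protocol article.

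- **Study Design** gives five grounds for exit in one list. The first reads "patients will exit from this clinical trial: (1) Serious deviation from clinical trial protocol". The second is "Due to serious adverse reactions, the drug must be stopped in advance" and the fourth is "Poor compliance and failure to use drugs as planned". Withdrawal of consent and loss to follow-up are the third and fifth. The list concerns exit from the trial, not from treatment.
- **Statistical Analysis** defines two sets: "The intention-to-treat (ITT) population will include all participants who have been randomly assigned", and "the per-protocol (PP) population will include all participants who accomplish the entire intervention".
- **Data Collection and Clinical Outcomes** and **Table 1** schedule the primary outcome, the visceral-to-subcutaneous fat area ratio, at transplantation and at months 3, 6, 9 and 12. Neither says that these measurements continue after exit.
- **Abstract** and **Study Design**: control receives triple immunosuppression alone, and the trial is open label. Randomization and Masking calls control the placebo group, but no placebo is described.
- **Sample Size Estimation** assumes one dropout rate of 20% for all arms.

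**The concern.** Intention-to-treat analysis protects the comparison only if outcomes are collected whatever happens to treatment. Here a conduct rule ends participation for patients who stop or misuse the drug, and a separate definition then counts them in the analysis set. They remain in the denominator, but their later scans are never taken.

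The loss is unlikely to be even across arms. A control patient has no study drug to stop because of a reaction or to fail to take. Read as referring to study drug, the second and fourth grounds can apply only in the two active arms. If patients doing worse are the ones who leave, those left in the active arms look better than the arms as randomised, and the bias favours the drugs. Safety and tolerability are also stated aims, and the rule ends observation of the patients who tolerate treatment least well.

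**Working it through.** **Inputs.** From Sample Size Estimation: control mean 0.83, SD 0.48, ratio halved on treatment (difference 0.83/2 = 0.415), 90% power, 5% significance (taken as two-sided), 28 per arm, 20% dropout, 35 per arm. The article gives no exit rate by arm or by reason, and no relation between exit and outcome. Those are assumptions below.

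**1. The plan's own figure.** n = 2 × [0.48 × (1.960 + 1.282) / 0.415]² = 28.1 per arm, matching the stated 28 to within rounding. Then 28 / 0.80 = 35, and 3 × 35 = 105. The sample size is not the problem.

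**2. What data exist for each exit.**

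| Ground for exit | Arms it can affect | Data after exit, as written |
|---|---|---|
| (1) serious deviation | all | none provided for |
| (2) drug stopped for serious reaction | active arms, if study drug is meant | none provided for |
| (3) consent withdrawn | all | none, unavoidable |
| (4) poor compliance | active arms, if study drug is meant | none provided for |
| (5) lost to follow-up | all | none, unavoidable |

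Grounds (1), (2) and (4) are avoidable losses created by the rule. Measurements before exit survive: a patient leaving in month 7 has baseline, month-3 and month-6 scans.

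**3. Effect in those remaining against effect in all randomised.** Assume that a fraction q of an active arm stops and gains nothing, while the rest gain the full 0.415. The all-randomised effect is 0.415 × (1 − q):

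- q = 10%: 0.374
- q = 20%: 0.332
- q = 30%: 0.291

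Those remaining show 0.415 throughout, which is larger by a factor 1/(1 − q): 11%, 25% and 43%.

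**4. Selective exit with no true effect.** Simulation of one active arm against control: 35 per arm, SD 0.48, two-sample t-test at 5%. Control loses 3 at random. The active arm keeps 28. Exiting patients are treated as wholly missing, and exit depends on a score correlated 0.3 or 0.5 with a worse ratio.

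| Active-arm losses | Correlation | Bias | Type I error |
|---|---|---|---|
| 7 selective | 0.3 | about -0.05 | about 7% |
| 7 selective | 0.5 | about -0.08 | about 11% |
| 4 selective, 3 random | 0.3 | about -0.03 | about 6% |
| 4 selective, 3 random | 0.5 | about -0.05 | about 7% |

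With zero correlation, type I error is about 5%. The harm therefore comes from selective exit, not from lost numbers.

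A closed-form check: let 20% of the active arm exit with a ratio 0.5 SD worse than completers, and observe control fully. Bias in size is 0.20 × 0.5 × 0.48 = 0.048. The standard error is 0.48 × √(1/35 + 1/28) = 0.122, and type I error is 6.8%. This agrees with the first row.

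**5. Power if everyone is followed.** Two-sample t-test, difference 0.332, SD 0.48: 81% with 35 per arm, 78% with 32, 76% with 31 and 72% with 28.

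**The case against.** The strongest reply has four parts.

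- **Earlier scans are kept.** A reader might infer that exiting patients contribute no outcomes, or that both analysis sets shrink to compliant completers. The text does not support either. The ratio is measured repeatedly, the intention-to-treat set still contains these patients, and scans before exit are available. Only later data are lost. Treating exiting patients as wholly missing therefore makes the simulation a pessimistic illustration. Laboratory data may also continue to accrue in routine records, so the loss is clearest for MRI.
- **The imbalance is inferred.** Grounds (1), (3) and (5) apply to every arm, and the drugs in ground (4) could include the immunosuppressants that all patients take. A reader might take the concentration in the active arms as stated. It is only probable.
- **The 20% dropout covers more than these rules.** It includes consent withdrawal and loss to follow-up, which no redrafting removes. That is why the case of 4 selective exits stands beside the case of 7. The correlations have no source in the article.
- **The gap between 0.415 and 0.332 is a difference of estimand.** It becomes an error only if the effect in those remaining is reported as the all-randomised effect.

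All four stand as limits on size. A reader might also fault the article for not naming a primary analysis set or a missing-data method. Those may be settled in an analysis plan that is not shown, and they form no part of this point. The exit rule is different: it is a printed conduct rule that decides which scans exist, and no later analysis plan can recover scans that were not taken.

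**Conclusion.** The point holds in this form. The exit list ends trial participation for serious deviation, stopped drug and poor compliance, and the article provides for no MRI afterwards. The all-randomised set therefore lacks later primary-outcome data for these patients. The losses probably fall mainly on the two active arms, and the contrast is biased if exit is related to outcome.

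The size is illustrative. Bias is about -0.03 to -0.08 and two-sided type I error about 6% to 11%. This rests on no true effect, 4 or 7 selective exits out of 35, correlation 0.3 or 0.5, and exiting patients wholly missing. The direction favours the drugs only if patients doing worse are those who leave.

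**What to change.** In Study Design, separate stopping study drug from leaving the trial. State that only withdrawal of consent and true loss to follow-up end data collection. Patients meeting grounds (1), (2) or (4) stay on the 3, 6, 9 and 12-month MRI and laboratory visits. In Statistical Analysis, state that their data after stopping enter the intention-to-treat analysis. Whether and when study drug is stopped is a clinical matter and is left unchanged.

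The amendment is short, the visits are already scheduled, and enrolment stays at 105. It should be made before more patients exit. The price is a possibly diluted effect. For 0.332, power is about 81% only if all 35 per arm are followed. Consent withdrawal and loss to follow-up will still occur, so 76% to 78% (31 to 32 per arm) or 72% (28 per arm) may be nearer the truth.

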**Figure 1 F1:**
[figure not shown]
Patients selection.

### Procedures

Metformin is administered 500 mg twice daily orally from discharge based on the previous preliminary clinical trial (17). Empagliflozin is administered 25 mg once daily orally from discharge (18, 20). This will commence at randomization and continue for 12 months. The decision to continue with metformin beyond 12 months of follow-up is left to the discretion of the caring physician. In addition, during the follow-up, when kidney transplant recipients are diagnosed with PTDM, insulin therapy were adopted to reduce the glucose level at 6.1–6.7 mmol/L based on Chinese Management Guideline of post-transplantation diabetes mellitus after kidney transplantation (21).

Immunosuppressive regimen has been reported in our previous study (22). In brief, all participants will receive standardized triad immunosuppression, consisting of tacrolimus, mycophenolate mofetil/enteric-coated mycophenolate sodium, and steroids. Tacrolimus trough levels are measured by the enzyme multiplied immunoassay technique before breakfast and dose administration in the morning. Recommended tacrolimus trough levels are 5–10 ng/ml. MMF is started at 1000 mg one night before operation and maintained at 1000 mg twice daily with area under curve of mycophenolate mofetil maintained at 30–70 mg/h·L-1. If EC-MPS is selected, 720 mg is given the night before surgery and 720 mg bid thereafter. Methylprednisolone is injected intravenously at 500 mg during the operation and 200 mg per day 3 days after the operation. Then 60 mg prednisone is initiated, and gradually taper to 5–10 mg per day for maintenance.

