### Data Collection and Clinical Outcomes

Standard demographic, clinical and laboratory data (including medication details) will be collected prospectively from electronic medical records. Recipients are advised to receive routine follow-up weekly in months 0–3, every 2 weeks in month 4–6, monthly within 6–12 months, and every 3 months thereafter.

The general aim of this study is to determine the safety of metformin and empagliflozin in kidney transplant recipients and explore the role of metformin and empagliflozin treatment in improving metabolic profiles. Based on previous study, visceral-to-subcutaneous fat area ratio, evaluated by magnetic resonance imaging (MRI), is generally reported as a surrogate for metabolic risk and is markedly raised in patients with long-term exposure to steroids (23, 24). Hence, the primary outcome is the differences in the visceral-to-subcutaneous fat area ratio over 12 months among three groups. The visceral-to-subcutaneous fat area ratio will be measured at transplantation, and post-transplant 3, 6, 9, and 12 months. Kidney graft function will be evaluated when they receive routine follow-up. Secondary outcomes included glycometabolism (fasting plasma glucose, fasting insulin levels, 2-h post-prandial insulin levels, hemoglobin A1c, and insulin beta-cell function [indicated by the homeostasis model assessment of β cell function]), lipid metabolism (serum triglyceride, non-high-density lipoprotein, low-density lipoprotein, total cholesterol), inflammatory parameters (C-reactive protein, interleukin-6, and tumor necrosis factor alpha) (Table 1). We will also examine cardiovascular disease and microvascular complications, including the following: major adverse cardiovascular events; all-cause mortality; atherosclerotic cardiovascular (ASCV) death; hospitalization or death from coronary artery disease, ischemic stroke, or heart failure; observable background diabetic retinopathy; and diabetic peripheral neuropathy.

**Table 1 T1:** Routine follow-up.

**Visit**	**V0**	**V1**	**V2**	**V3**	**V4**
Time, days after kidney transplantation	−7day to 0 day	3 month	6 month	9 month	12 month
Participant-related information	×				
Informed consent	×				
History	×				
Inclusion/Exclusion	×				
Clinical examination	×	×	×	×	×
Efficacy and safety outcomes	×	×	×	×	×
Body weight	×	×	×	×	×
Height	×	×	×	×	×
Waist circumference	×	×	×	×	×
Visceral adipose tissue (VAT)	×	×	×	×	×
Subcutaneous adipose tissue (SAT)	×	×	×	×	×
VAT/SAT ratio	×	×	×	×	×

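### Insulin started at PTDM diagnosis alters the glycaemic secondary outcomes, while new-onset PTDM and insulin start are not outcomes themselves: a cheap improvement

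*Protocol article*

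**What the plan says.** All references are to the protocol article.

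- **Procedures.** The trigger is "during the follow-up, when kidney transplant recipients are diagnosed with PTDM"; the response is "insulin therapy were adopted to reduce the glucose level at" 6.1–6.7 mmol/L. No arm is exempted.
- **Study Design.** The exclusion of "pre-transplant diabetes" means that every participant is at risk of new-onset PTDM. Neither PTDM nor insulin start is among the five reasons for leaving the trial.
- **Data Collection and Clinical Outcomes.** The glycaemic secondary outcomes are "fasting plasma glucose, fasting insulin levels, 2-h post-prandial insulin levels, hemoglobin A1c, and insulin beta-cell function", the last "indicated by the homeostasis model assessment of β cell function". Table 1 schedules them at every visit. Diabetic retinopathy and peripheral neuropathy are also to be examined. New-onset PTDM, insulin start and insulin use appear in neither the outcome text nor Table 1.
- **Statistical Analysis.** The intention-to-treat set is everyone randomised; the per-protocol set is everyone who completes the intervention. "For clinical outcomes, analysis of covariance will be used to examine differences among three groups", with age and sex as example covariates. PTDM enters only through subgroups defined by the *risk* of PTDM, not by its occurrence.

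**The concern.** Insulin start happens after randomisation and depends on the outcome. If metformin or empagliflozin prevents PTDM, more control recipients are diagnosed and more receive insulin towards the same glucose range. Their later glucose and HbA1c then partly reflect that range, which pulls the arms together.

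HOMA-beta is built from fasting insulin and fasting glucose. It rises when treatment lowers glucose, and rises further if the assay picks up injected insulin. The event that would show the benefit directly, a PTDM diagnosis or the need for insulin, is not compared between arms.

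At stake is the trial's glycaemic conclusion. A drug that spares recipients diabetes could show only a small glucose difference, and an arm with more insulin users could show higher insulin and HOMA-beta values that are misread as better beta-cell function.

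**Working it through.** **The plan's own figure.** The sample size concerns the MRI ratio: control mean 0.83, SD 0.48, halved under treatment, so the difference is 0.415. Two-sided at 5% with 90% power, n = 2 × (1.960 + 1.282)² × 0.48² / 0.415² = 28.1 per group. Power at 28 is 89.9%, and 28 / 0.80 = 35. The stated 28 and 35 reproduce to rounding, and nothing below touches them.

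**Inputs for the illustration.** From the document: the range 6.1–6.7 mmol/L, midpoint 6.4. It is used here as fasting glucose, although Procedures says only glucose level. Assumed, because the document gives no values: PTDM in 25% of controls and 10% on drug; 5.5 mmol/L without PTDM; 7.5 to 9.0 mmol/L with PTDM left untreated.

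**Case A: the drug has no effect in recipients without PTDM.**
- Difference without insulin: (0.25 − 0.10) × (7.5 − 5.5) = 0.30, up to 0.15 × (9.0 − 5.5) = 0.525.
- Difference with insulin: 0.15 × (6.4 − 5.5) = 0.135.
- Retained: 0.135/0.30 = 45% to 0.135/0.525 = 26%, so 55–74% is lost.
- The incidences cancel: retained = (6.4 − 5.5)/(untreated − 5.5).
- Other assumptions (5.3 without PTDM; 7.5, 8.5 or 10.0 untreated) retain 50%, 34% and 23%.

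**Case B: the drug also lowers glucose by 0.3 mmol/L in recipients without PTDM (5.2 versus 5.5).**
- Let u be glucose in PTDM. Control mean: 0.25u + 0.75 × 5.5. Drug mean: 0.10u + 0.90 × 5.2. Difference: 0.15u − 0.555.
- Untreated: 0.570 at u = 7.5 and 0.795 at u = 9.0. Treated: 0.405 at u = 6.4.
- Lost: 0.165/0.570 = 29% to 0.390/0.795 = 49%.
- The loss now depends on incidence. With untreated PTDM at 7.5, at 10% versus 5% the difference is 0.05u + 0.01, and 0.055/0.385 = 14% is lost. At 40% versus 20% it is 0.20u − 0.86, and 0.22/0.64 = 34% is lost.

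**HOMA-beta.** Standard form: 20 × insulin (mU/L) / (glucose − 3.5). Insulin values are assumed.
- Insulin 8, glucose 8.5: 160/5.0 = 32.
- Insulin 8, glucose lowered to 6.4: 160/2.9 = 55.
- Measured insulin 20 because injected insulin is detected, glucose 6.4: 400/2.9 = 138.

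To see what this does to arm means, take recipients without PTDM at insulin 8 and glucose 5.5, so 160/2.0 = 80, with 25% versus 10% PTDM:
- Untreated PTDM at 32: control 68.0, drug 75.2; drug higher by 7.2.
- Treated, only glucose changed (55.2): control 73.8, drug 77.5; drug higher by 3.7.
- Treated, injected insulin detected (137.9): control 94.5, drug 85.8; *control* higher by 8.7.

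The order reverses only in the last case, which depends on the assay.

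**PTDM as an outcome.** Power at 35 per arm, two-sided 5%, normal approximation: Φ{[|p1 − p2| − 1.96√(2p̄(1 − p̄)/n)] / √[(p1(1 − p1) + p2(1 − p2))/n]}. For a halving this gives 21% (20% versus 10%), 32% (30% versus 15%) and 45% (40% versus 20%).

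**The case against.** **It belongs in the analysis plan.** Rules for values measured after insulin start are commonly left to an analysis plan, which is not shown, and a comparison of everyone as actually treated is a legitimate treatment-policy estimand. Both points stand, so missing handling rules alone are no finding. The outcome list, however, is set out in the article, and it leaves out the event that triggers the insulin.

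**The benefit is hidden and the insulin data are invalid.** A reader might infer this, but the documents do not support it. In every glucose illustration above the difference keeps its direction, and an effect in recipients who never need insulin still shows. The problem with insulin and HOMA-beta concerns samples taken under insulin, not all participants, and the article describes no insulin assay.

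**The loss is a fixed 55–74%.** That holds only in Case A. Both drugs are glucose-lowering, so Case B is a fair alternative. The benchmark is also hypothetical: diagnosed PTDM left untreated is something this trial would never observe.

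**PTDM is low-powered and not the trial's focus.** The power is low, so PTDM cannot carry a claim alone. But the article already lists diabetic complications as outcomes in people without diabetes at entry, and diabetes onset is the more natural outcome to report.

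**Dropping samples after insulin start biases too.** Correct: it removes the recipients with the worst beta-cell function, and more of them from the arm with more PTDM. The fix does not rest on it.

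**Conclusion.** The point holds as a low-cost improvement to the secondary outcomes. As written, the plan compares glucose, HbA1c, insulin and HOMA-beta values that the protocol's own insulin rule alters, and it does not compare how often that rule is triggered. The part of a glucose or HbA1c difference that comes from preventing PTDM is attenuated and may be masked. HOMA-beta under insulin can rise without better beta-cell function, and measured insulin may include injected insulin to the extent that the assay detects it.

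The size cannot be fixed from the document. Under the stated assumptions the loss in fasting glucose is 55–74% with no drug effect outside PTDM and 29–49% with a 0.3 mmol/L effect there; only in the first case is it independent of PTDM incidence. It shrinks as PTDM becomes rarer or the effect outside PTDM larger. The insulin rule itself is not questioned.

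**What to change.** **Data Collection and Clinical Outcomes.** Add new-onset PTDM or insulin start by month 12 as a secondary outcome, using the diagnosis that already triggers insulin. Report the proportion per arm with risk difference and 95% CI, and label it supportive in view of the power of about 21–45%.

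**Statistical Analysis.**
- Keep the ANCOVA of glucose and HbA1c on all participants, and report it beside the proportion on insulin in each arm.
- Add a sensitivity analysis for glucose, HbA1c and HOMA-beta that ranks insulin-treated recipients worst.
- State that fasting insulin, 2-h insulin and HOMA-beta measured under insulin are not interpreted as endogenous function.
- If results from pre-insulin samples are shown, say that they selectively omit the worst recipients, and read them beside the PTDM comparison.

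**Cost.** One extra low-powered outcome and some extra analysis. Laboratory data and medication details are already to be collected, so the main task is to record the date of diagnosis or insulin start consistently. The sample size and the primary analysis do not change.
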